## Abstract

**Background:**

Adherence to antihypertensive drugs (AHDs) is important for adequate blood pressure control. Not taking these drugs as prescribed is one of the main underlying causes for resistant hypertension (RH), which in turn leads to an increased risk of cardiovascular events, stroke and kidney damage. Therefore, correct identification of patients that are non-adherent to AHDs is crucial to improve clinical outcome. For this goal, therapeutic drug monitoring is the most reliable method. The primary objective of this trial is to investigate whether monitoring of drug concentrations with a dried blood spot (DBS) sampling method combined with personalised feedback leads to a decrease in prevalence of RH after 12 months due to an increase in adherence. Secondary objectives include the difference over time in the number of required AHDs as well as the defined daily dose (DDD). Lastly, the cost-utility of SoC versus the intervention in RH is determined.

**Methods:**

This is a multi-centre single-blinded randomised controlled trial (RHYME-RCT). First, at an eligibility visit, DBS sampling, to monitor drug concentrations in blood, and a 24-h ambulatory blood pressure measurement (24-h ABPM) are performed simultaneously. Patients with a daytime systolic blood pressure (SBP) > 135 and/or diastolic blood pressure (DBP) > 85 mmHg are randomised to SoC or intervention + SoC. The intervention is performed by the treating physician and includes information on drug concentrations and a comprehensive personalised feedback conversation with the use of a communication tool. The follow-up period is one year with visits at 3, 6 and 12 months randomisation and includes 24-h ABPM and DBS sampling.

**Discussion:**

This will be the first trial that focusses specifically on patients with RH without taking into account suspicion of non-adherence and it combines monitoring of AHD concentrations to identify non-adherence to AHDs with a comprehensive feedback to improve non-adherence. Furthermore, if this trial shows positive outcomes for the intervention it can be directly implemented in clinical practice, which would be a great improvement in the treatment of RH.

*Trial registration*. RHYME-RCT is registered in the Dutch Trial Register on 27/12/2017 (NTR6914) and can be found in the International Clinical Trials Registry Platform.

**Supplementary Information:**

The online version contains supplementary material available at 10.1186/s12872-023-03114-0.

## Introduction

Non-adherence to antihypertensive drugs (AHDs) is one of the most important causes of uncontrolled blood pressure. Uncontrolled blood pressure leads to high costs and suboptimal cardiovascular prevention [1–4]. When patients have uncontrolled blood pressures despite a medication regimen of AHDs from at least three classes including a diuretic, they are defined as having resistant hypertension. Resistant hypertension leads to more frequent outpatient clinic visits, more additional diagnostic tests and more hospitalizations because of a hypertensive emergency, stroke or myocardial infarction, and thus has a large individual and societal impact [2–4]. The majority of patients with resistant hypertension (estimated 40–60%) have a problem with adherence to their medication explaining their assumed resistance to therapy [5–10].

Identifying non-adherence and, more importantly, improving non-adherence is of major importance to reduce disease burden and costs[11–14]. For the identification step many tools are available and most have been investigated in previous interventions trials [15, 16]. The more reliable these identification methods become, the more invasive and costly they are. Electronic pill dispensers (also known as MEMS: Medication Events Monitoring Systems) are considered the gold standard for identification of non-adherence, but this method is not available on a large scale amongst all due to relatively high costs [2, 17, 18]. Recent research also showed the value of monitoring drug concentrations in blood or urine by (ultra-high) liquid chromatography-mass spectrometry (UHPLC-MS/MS) [19–21]. Although this is an objective and reliable method to determine non-adherence, the use in clinical practice is still limited [7, 9, 10, 22].

To improve the clinical usability of measurement of drug concentrations in blood, we have developed a dried blood spot (DBS) sampling method for AHDs. With this method, blood can easily be obtained by a finger or heel prick (similar to the diagnosis of inborn errors of metabolism in new-borns) [23]. DBS sampling enables immediate sampling in the office when non-adherence is expected without an additional visit to the blood sampling unit [23]. Using this method, non-adherence can be indisputably determined and (potentially undetectable) drug concentrations can be discussed with the patient. However, identification of non-adherent patients, will not directly improve non-adherence or blood pressure.

Therefore, consecutive steps are necessary. For the second step, improving non-adherence, behavioural interventions seem to be most successful [16]. Therefore, we developed a communication tool involving assessing barriers to adherence. Subsequently a personalised solution addressing the specific identified barrier of the patient can be realized. We think that the combination of monitoring drug concentrations with a behavioural intervention is a potential solution for solving the non-adherence issue.

Therefore, we aim to perform a randomised controlled trial to investigate whether showing patients the results of their drug concentration measurements combined with a behavioural change technique, is an effective intervention to improve adherence and thereby decreases the number of patients with assumed resistant hypertension.

## Methods

RHYME-RCT (ICTRP, NTR6914, https://trialsearch.who.int/Trial2.aspx?TrialID=NTR6914) is a randomised, multicentre, single-blinded, controlled trial to improve non-adherence to AHDs and reporting is based on the ESPACOMP Medication Adherence Reporting Guidelines (EMERGE) [24]. The study design and visit schedule are shown in Fig. 1 and Additonal file 1: Table S1.

**Fig. 1 Fig1:**
[figure not shown]
Study design RHYME-RCT trial to improve non-adherence to antihypertensive drugs and thereby blood pressure in patients with resistant hypertension

### Subjects

#### Inclusion and exclusion criteria

Patients will be recruited from vascular, cardiology and nephrology outpatient clinics of 11 hospitals including two university hospitals. Patients are eligible for participation if they fulfill the criteria of resistant hypertension, use at least two AHDs for which DBS-analysis are available, are 18 years or older and are able to provide informed consent. Due to the large population of people orginating from Turkey in Rotterdam, the patient information leaflet is made available in both the Dutch and Turkish language.

Resistant hypertension is defined as having an office BP of > 140 mmHg (systolic) and/or 90 mmHg (diastolic) or, if available, a 24-h ambulatory blood pressure measurement (24-h ABPM) daytime BP of > 135 mmHg and/or 85 mmHg despite a medication regimen of AHDs in the maximal tolerable dose of at least three AHDs from different drug classes, including a diuretic, or at least four AHDs from different drug classes. In Table 1 the minimal drug dose needed at time of the inclusion and the lower limit of detection of each included drug are shown. DBS analysis includes the following AHDs and active metabolites: enalapril and enalaprilate, perindopril and perindoprilate, irbesartan, valsartan, losartan and losartan-carboxylic acid (losartan-CA), hydrochlorothiazide, bumetanide, spironolactone and canrenone, amlodipine, barnidipine, nifedipine, metoprolol and doxazosin [25, 26].

**Table 1 Tab1:** Overview antihypertensive drugs included in the RHYME-RCT trial

Antihypertensive drug [metabolite]	Minimal drug dose for inclusion (mg)	LLOD (μg/L) [25]
Amlodipine	5	17.1
Barnidipine	10	2.1
Bumetanide	1	4.0
Doxazosin	4	18.1
Enalapril	20	0.4
[Enalaprilat]	–	1.1
Hydrochlorothiazide	12.5	40.2
Irbesartan	150	7.7
Losartan	50	1.7
[Losartan-CA]	–	2.6
Metoprolol	50 CR or 25 mg two times daily (normal release)	0
Nifedipine	30	3.5
Perindopril	4	0.7
[Perindoprilat]	–	1.3
Spironolactone	12.5	5.2
[Canrenone]	–	26.8
Valsartan	80	21.3

*CA* carboxylic acid; *CR* controlled release, *LLOD* lower limit of detection

Patients are excluded from participation if they are not able to give informed consent, have end-stage kidney disease (eGFR < 15 ml/min/m^2^), insufficient understanding of the Dutch or Turkish language or if secondary forms of hypertension are expected but have not been excluded. Patients with secondary forms of hypertension primarily treated with AHDs such as primary aldosteronism caused by bilateral hyperplasia can be eligible for participating in the trial.

This study is approved by the Institutional Review Board (IRB) of the Erasmus MC, University Medical Centre, Rotterdam, the Netherlands (MEC-2018–027).

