#### Standard of care (SoC) alone

SoC includes visits at 3 (t3), 6 (t6), and 12 (t12) months follow-up, with preferably a 24-h ABPM, and otherwise an automated office blood pressure (AOBP) combined with DBS sampling. In the SoC arm the results on drug concentrations are not reported during the study and are only used for resarch purposes.

The results of the blood pressure measurements are available for all healthcare providers. If deemed necessary by the treating physician it is allowed to schedule extra appointments outside the research visits. Also, it is allowed to make changes to the AHD treatment during every visit, without restriction with regard to the choice or dose of drugs. These changes are registered at every visit. If a patient switched to AHDs that are not included in the TDM method, only blood pressure measurements are included in the analysis.

Patients are allowed to make life style changes during the trial. These life style changes can possibly influence the adherence outcome and is therefore taken into account in our power calculation.

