### Methods of measurement

#### Blood pressure measurement

24-h blood pressure is recorded with the available ABPM device on site. All devices have to be approved for use in clinical practice. Measurements are performed with the device attached to the non-dominant arm if possible. Patients are instructed to relax their arm during the measurements and to pursue their normal daily activities. During the 24-ABPM patients are also asked to write down physical and stressful activities in a diary, as well as their true sleeping times. Depending on the hospital, BP is measured at a 20-min or 30-min interval during daytime and a 30-min or 60-min interval at night-time. Measurements are included if > 50% of the 24-h measurements was successful which includes at least 20 valid awake measurements and 7 valid asleep measurements [28, 29]. If a patient is eligible for the study because of a 24-h ABPM ≥ 135 and/or 85 mmHg measured for clinical purposes and the fingerprick is obtained within 4 weeks after this measurement, it is a allowed to use this ABPM measurement as inclusion criterion. However, an AOBP has to be performed at time of the fingerprick and needs to be ≥ 140 and/or 90 mmHg. If a patient does not want to do a 24-ABPM during the eligibility visit, they are excluded from participation. At all the follow-up visits, the 24-h ABPM can be replaced with a 30-min AOBP upon reasonable request of the patient as stated before.

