### Study endpoints

#### Primary objective

Our primary objective is to determine whether an intervention that consists of monitoring AHD concentrations combined with personalised feedback added to SoC leads to a larger decrease in the prevalence of RH after 12 months of follow-up than SoC alone.

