#### Statistical analysis

Continous variables with a normal distribution are described as mean value ± one standard deviation (SD), and otherwise as median value (25th–75th percentile). Normality is tested by the Shapiro–Wilk test. Categorical variables are described as numbers and percentages. Within group changes in percentage non-adherence and RH from t0 to t12 are evaluated by McNemar tests. We use a Chi^2^-test to study change-differences in non-adherence and RH between patients randomised to the intervention + SoC versus SoC alone.

The defined daily dose (DDD) is the assumed average maintenance dose of a drug used for its main indication in adults [36]. These averages are used to determine how many times the DDD for each individual drug is used. Subsequently, the averages of these DDDs are calculated for t0 and t12 for individual patients.

Differences in blood pressure and DDDs over time within the same arm are tested by means of a paired sample t-test and differences between patients randomised to the intervention + SoC versus SoC alone with a independent samples t-test.

We will perform an intention-to-treat analysis, including all randomised patients, as well as a per-protocol analysis, including the patients with available measurements at t0 and t12, and one of t3 and t6.

Data from the questionnaires are used for the cost-effectiveness and cost-utility analysis of the intervention. A cost-utility analysis will be performed with quality adjusted life years (QALY) for a lifelong period. The QALYs will be calculated based on the EQ-5D-5L summary score. Cost-effectiveness from a healthcare perspective will be calculated for a 1-year period using the number of patients fulfilling the definition of resistant hypertension after 12 months (the primary outcome measure).

All p-values are two-sided, and a value of < 0.05 is considered statistically significant.

We used the SPSS version 24.0 for Windows (IBM Corp, Armonk, NY), and GraphPad Prism 9.3 software (GraphPad Software, La Jolla, CA) for analysis.

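### The 12-month primary outcome keeps the drug-regimen clause of the entry definition, so a patient whose blood pressure is still uncontrolled can be scored as no longer resistant

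*Protocol article*

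**What the plan says.** All references are to the protocol article.

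- **Primary objective.** The question is whether the intervention "leads to a larger decrease in the prevalence of RH after 12 months of follow-up than SoC alone".
- **Statistical analysis.** In describing the cost-effectiveness analysis, this section identifies the outcome as the "number of patients fulfilling the definition of resistant hypertension after 12 months (the primary outcome measure").
- **Inclusion and exclusion criteria.** This is the only operational definition of RH. Its BP part is "having an office BP of > 140 mmHg (systolic) and/or 90 mmHg (diastolic) or, if available, a 24-h ambulatory blood pressure measurement" with daytime limits of 135/85 mmHg. Its regimen part is "despite a medication regimen of AHDs in the maximal tolerable dose of at least three AHDs from different drug classes, including a diuretic"; a regimen of four or more classes is the stated alternative. Both parts must hold. No separate definition is given for follow-up.
- **Standard of care (SoC) alone.** After randomisation "it is allowed to make changes to the AHD treatment during every visit, without restriction with regard to the choice or dose of drugs". The Randomisation section says that health care providers are told the allocation.
- **Blood pressure measurement.** A patient who declines ambulatory measurement (ABPM) at the eligibility visit is excluded. Later, "At all the follow-up visits, the 24-h ABPM can be replaced with a 30-min AOBP upon reasonable request of the patient". AOBP is automated office BP.

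**The concern.** A definition that works for selecting patients can fail as an outcome. At entry, the regimen clause makes sure that raised BP is not simply undertreatment. At 12 months the same clause is open to change by post-randomisation treatment decisions. A patient can leave the RH category by reaching the BP target, which the trial wants to detect, or by no longer satisfying the clause while BP stays high. The chi-square comparison cannot tell the two apart.

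The sample size section attributes the whole expected fall in RH to better adherence. The regimen route bypasses that mechanism, and the decisions behind it are made by people who know the arm.

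**Working it through.** **Inputs from the article.** RH at 12 months 90% (SoC) and 80% (intervention + SoC); 196 patients per arm; two-sided α 0.05; power 80%; 1:1 allocation; baseline non-adherence 50%, with relative falls of 20% and 40%.

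**Assumed input.** q is the share of patients with uncontrolled BP who are scored as not RH only because the regimen clause fails. The documents give no value, so a range is shown.

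**Step 1: the plan's own figures.** The rates follow from 1 − 0.5 × 0.2 = 0.90 and 1 − 0.5 × 0.4 = 0.80. With unpooled variance,

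n = [0.9 × 0.1 + 0.8 × 0.2] × (1.960 + 0.842)² / 0.1² = 0.25 × 7.849 / 0.01 = 196.2 per arm.

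The pooled-variance version gives 199. The stated 196 is reproduced and is not in question. Power at 196 per arm, with pooled variance under the null, is

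Φ{[|p₁ − p₂|√n − 1.96√(2p̄(1 − p̄))] / √[p₁(1 − p₁) + p₂(1 − p₂)]} = Φ{[1.400 − 0.990] / 0.500} = 79.4%.

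**Step 2: apply the rule to one patient.** Take BP of 150/95 mmHg at both visits, on three classes with a diuretic at entry, and on two classes (or three without a diuretic) at 12 months. The BP part is met both times. The regimen part is met only at entry. The patient is scored as not RH although BP has not moved.

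**Step 3: equal reclassification, true uncontrolled BP 90% vs 80%.** Observed RH in each arm is the true share × (1 − q).

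| q in both arms | RH, SoC vs intervention | Power at 196 per arm | n per arm for 80% power (pooled) |
|---|---|---|---|
| 0% | 90.0% vs 80.0% | 79.4% | 199 |
| 5% | 85.5% vs 76.0% | 66.6% | 270 |
| 10% | 81.0% vs 72.0% | 55.7% | 348 |
| 20% | 72.0% vs 64.0% | 39.6% | 533 |

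The difference shrinks by the factor (1 − q), and the variance grows as the proportions move away from 1.

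**Step 4: unequal reclassification.** The planned 10 points are 0.10 × 196 ≈ 20 patients per arm. Since 0.10 / 0.90 = 11.1%, reclassifying 11.1% of a group that is 90% uncontrolled moves its RH rate from 90% to 80%.

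| True uncontrolled BP, SoC vs intervention | q, SoC vs intervention | RH scored | Chance of a significant result favouring the intervention |
|---|---|---|---|
| 90% vs 90% | 2% vs 5% | 88.2% vs 85.5% | 12.1% (2.5% if q is equal) |
| 90% vs 90% | 0% vs 5% | 90.0% vs 85.5% | 27.3% |
| 90% vs 90% | 0% vs 11.1% | 90.0% vs 80.0% | 79.4% |
| 90% vs 80% | 5% vs 0% | 85.5% vs 80.0% | 30.1% |
| 90% vs 80% | 10% vs 0% | 81.0% vs 80.0% | 4.4% |

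The first three rows create an effect where none exists. The last two hide a real one.

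**Step 5: BP method.** Entry status rests on daytime ABPM at 135/85. At follow-up an AOBP reading may stand in, and the definition's non-ambulatory limit is 140/90. The article also applies that limit to AOBP in one entry pathway, where "an AOBP has to be performed at time of the fingerprick and needs to be ≥ 140 and/or 90 mmHg". So a patient's status can be judged by different methods and cut-offs at the two time points. The Abstract and the inclusion criteria write the limits with >, whereas the Blood pressure measurement section writes ≥.

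**The case against.** **The reuse is inferred.** No sentence says that the inclusion definition applies at 12 months, and a fuller protocol or analysis plan could contain a scoring rule. This is a fair caveat. However, the article itself ties the primary outcome to the definition of RH and offers only one.

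**Bias towards the intervention.** A reader might infer this, because only intervention-arm providers see the drug concentrations and agree tailored solutions. The documents do not support it. The secondary objectives ask whether the number of drugs differs between arms and state no direction. A drug that is prescribed but undetected is still part of the regimen. A patient who needs fewer drugs because BP is controlled is a genuine success. Only patients who stay uncontrolled and also drop out of the regimen clause matter, and nothing says how many there are or in which arm.

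**The change of method.** A reader might also infer that switching to AOBP produces successes outright, since a systolic reading of 138 mmHg is above one limit and below the other. That assumes both methods read alike in the same patient, which the article does not say. The two cut-offs are paired with different methods, and a diastolic value above 90 would keep the patient in RH under either. The net direction is unknown.

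**Existing safeguards.** Drug changes are registered at each visit, drug numbers and daily doses are compared, and BP is compared between arms. A regimen-driven result might therefore be noticed. These analyses help interpretation but do not correct the primary test.

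**RH is the declared target.** A regimen clause belongs to the concept of RH, so an outcome on BP alone answers a slightly different question. That is true, and it is the price of the fix.

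**Conclusion.** The point stands as a defect in how the primary outcome is scored: the rule as written can record success without any fall in BP, through decisions taken after randomisation by providers who know the allocation. This follows from the text and needs no assumption about rates.

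Its size does depend on assumed rates. Equal reclassification of 5% to 10% cuts power from about 79% to about 67% to 56%. Reclassification of about 11% of uncontrolled patients in one arm only matches the entire planned effect, in either direction. It cannot be concluded that the trial is biased in favour of the intervention. The change of BP method is a secondary issue of unknown net direction, and the inequality sign is editorial.

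**What to change.** Change the scoring only; no treatment rule is affected.

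1. Define the 12-month primary endpoint as BP above the plan's own cut-off in every randomised patient, whatever the number, class or dose of drugs at that visit.
2. Keep RH by the full definition (BP plus regimen) as a secondary endpoint.
3. Make daytime ABPM the primary BP method. The Discussion already mentions daytime measurement as an alternative for patients who might otherwise drop out.
4. Report AOBP use by arm, and run a sensitivity analysis for patients with AOBP only, for example classified at the plan's office cut-off versus ABPM status imputed.
5. Reconcile > and ≥ between the Abstract, the inclusion criteria and the Blood pressure measurement section.

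The cost is a wording change before unblinding plus one sensitivity analysis, using BP data already collected. If 90% vs 80% is still expected, the sample size stays at 196 to 199 per arm. The downside is that the endpoint becomes uncontrolled BP among patients enrolled with RH, rather than RH by its full definition.

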#### Withdrawal

Patients are allowed to withdraw from the trial at any time without a statement of reason. However, when a reason is given by the patient, this will be noted. Also, investigators can decide to withdraw a subject from the study for urgent medical reasons. Data from withdrawn patients will be included if possible. Patients that withdraw before reaching 12 months follow-up will be replaced.

### Study design

Eligible patients are informed about the trial by the treating physician. Patients are told that with the fingerprick drug concentrations in blood are measured. However, the term adherence will not be mentioned to the patients and is not included in the patient information leaflet. If the patient is interested in participation, written information will be provided. After at least one week the patient is called by the researchers, to answer patients’ questions regarding study participation. When verbal consent is given, an eligibility visit is scheduled. At this eligibility visit, called t0, written informed consent will be obtained, a 24-h ABPM is performed and simultaneously a finger prick for therapeutic drug monitoring (TDM) is performed. Medication is not standardised prior to inclusion.

Based on the results of the 24-h ABPM during t0, patients are either excluded or randomised to a ‘personalised feedback conversation’ (intervention) added to standard of care (SoC) or SoC alone (Fig. 1).

After randomisation the treating physician is asked to estimate if the patient was adherent to AHDs or not, to determine if there is any bias in selecting patients. The selection of patients is based on blood pressure and thereby resistant hypertension, but physicians can potentially approach only patients they expected to be non-adherent. The adherence estimation is always performed before outcomes on non-adherence are reported (applicable for the intervention + SoC arm).

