#### Randomisation

The hospitals participating in the trial are divided into strata. For each stratum random block randomisation is performed in blocks of 4–6. Within these blocks patients are randomly assigned to either the SoC alone or intervention + SoC arm in a 1:1 ratio. Results on randomisation are communicated to the health care providers.

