#### Blinding

The measurements performed to determine non-adherence are only reported to the health care providers when patients ware randomised to the intervention + SoC arm. Measurements from the control arm are only available after completion or withdrawal of the study. Also, the laboratory that performed the measurements are not aware of the randomisation or which ID belonged to which patient. Only the coordinating researcher is not blinded and thereby is able to report the results from the intervention + SoC arm patients to the right physician. The coordinating researcher does not perform the actual intervention.

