#### Intervention + SoC

The intervention can be described as a ‘comprehensive personalised feedback conversation’ added to SoC, and consists of a three-step method [27]. For this comprehensive converstation extra consultation time was planned for phycisians that usually only have 10-min consultations. When patients are going to a nurse practioner for blood pressure control, no extra time will be planned while they already have 30-min consultations.

First, results of the AHD concentrations measured with UPLC-MS/MS are reported back to the healthcare provider.

In the second step of the intervention, the treating physician or nurse practitioner have to relay the findings of the drug concentrations in a non-accusatory way. To support and guide exploration of reasons for non-adherence a communication tool is developed by a sociologist and psychologist as previously discribed by Peeters et al [27]. By examining the reasons for non-adherence, tailored solutions can be agreed upon. Therefore, in the final step, based on the individualised determinants of adherence and potential solutions, a plan is made to improve adherence to AHDs.

All health care providers have to follow a training beforehand to improve their communication skills. This training includes a 90 min lecture on the theory around adherence and how to improve this with communication. After the lecture, participants have one hour to practice the feedback conversation with one another, coached by a sociologist or psychologist. Also, a digitial version of the training is available as a booster.

Patients in the intervention + SoC arm receive personalised feedback at t0 and t3. At t6 and t12 results on drug concentrations are still reported to the treating health care providers, but not communicated to the patient to determine sustainability of the earlier intervention (Fig. 1).

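### The physician's adherence estimate, meant to check for selection bias, is asked only after randomisation and may not reflect the belief held when the patient was approached (minor)

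*Protocol article*

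**What the plan says.** The protocol article, Methods, Study design, sets the timing: "After randomisation the treating physician is asked to estimate if the patient was adherent to AHDs or not". The same sentence gives the purpose, "to determine if there is any bias in selecting patients", and the next one names the mechanism feared: "physicians can potentially approach only patients they expected to be non-adherent".

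One protection is stated: "The adherence estimation is always performed before outcomes on non-adherence are reported (applicable for the intervention + SoC arm").

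The Randomisation section adds: "Results on randomisation are communicated to the health care providers". Under Intervention + SoC, those same providers act on the allocation: "the treating physician or nurse practitioner have to relay the findings of the drug concentrations in a non-accusatory way".

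**The concern.** A check on selection should capture what the physician believed when choosing whom to approach. Here the question comes several steps later, after information has arrived that could colour the answer. The authors saw that later information can contaminate the estimate, because they require it before the drug levels are reported. They did not extend that protection to the ABPM result or to knowledge of the arm.

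At stake is the support for a claim about the trial population. The abstract and the Discussion present the trial as recruiting on blood pressure and prescribed drugs, regardless of whether the physician suspects non-adherence. The estimate is the article's check on whether that held in practice at the point of approach. If it is unreliable, readers have less basis for judging whom the results apply to.

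**Working it through.** No figure in the article bears on this point, so the check is a comparison of the sections in time order.

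**Sequence, from Study design, Randomisation and Blinding**

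1. The treating physician informs an eligible patient. The feared selection acts here.
2. After at least a week the researchers telephone. If the patient agrees verbally, t0 is scheduled.
3. At t0, written consent, the 24-h ABPM and the finger prick take place.
4. The ABPM result leads to exclusion or randomisation.
5. The allocation is communicated to the providers, at a time the article does not state.
6. The physician is asked for the estimate, at some point after step 4.
7. In the intervention arm only, drug levels are reported to the provider.

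**What the safeguard covers.** It fixes step 6 before step 7. It does not place step 6 before step 4, and it does not order steps 5 and 6. The physician may therefore answer knowing that daytime pressure is raised on ABPM, and possibly knowing the arm.

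**Is the physician blind to the arm?** The Blinding section says "Only the coordinating researcher is not blinded". In context this concerns the drug measurements. It cannot mean that physicians are unaware of allocation, since they or the nurse practitioners deliver the feedback.

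**Who is rated.** Patients excluded at step 4 never reach step 6. The estimate describes only randomised patients, although the selection of interest acted on everyone approached.

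**How a shift would affect the check.** The relevant quantity is the proportion suspected among all those rated. Let the true proportion be p, and let the answers shift by a in one arm and b in the other. Patients are "randomly assigned to either the SoC alone or intervention + SoC arm in a 1:1 ratio", so the pooled proportion is

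[(p + a) + (p + b)] / 2 = p + (a + b)/2.

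If the shifts are equal and opposite (b = −a), the pooled figure stays at p. If they are unequal in size, or run in the same direction, it moves by (a + b)/2. An effect of the ABPM result or of the elapsed time could act the same way in both arms and would not cancel. The article gives no values for a or b, so the size and direction of any distortion are unknown.

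**What does not change.** The estimate is not an input to the sample size of 2 × 196 = 392. It is not among the objectives, and it is not in any test listed under Statistical analysis.

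**The case against.** The strongest reply is that the worst contaminant is already handled: an estimate made after seeing the drug levels would be worthless, and the article rules that out. Knowing the arm says nothing about whether a patient takes the drugs. The article also does not say in so many words that the physician knows the allocation when answering. All of this stands. It limits the point to a risk that the text leaves open, and it is why the heading says *may*.

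It is also fair that the claim of selection on blood pressure does not rest on this estimate alone. The eligibility criteria and the ABPM requirement before randomisation make no use of suspected non-adherence. The estimate is an additional check on who was approached.

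A reader might infer more: that the late timing would create a false difference between arms, or would spoil the estimate as a subgroup factor or covariate. The documents do not support this. No between-arm test of the estimate is described, and no subgroup or covariate use of it. Equal and opposite shifts would also leave the pooled proportion unchanged, as shown above.

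Two objections concern the remedy. Asking at invitation could prompt the physician to think about adherence while choosing patients, and so influence the very selection under study. Asking before any ABPM result is not always possible, because the Blood pressure measurement section allows a clinical ABPM from up to 4 weeks before the finger prick. Both are sound, but neither applies to a question asked at t0 before randomisation, with the ABPM condition applied where it can be met.

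**Conclusion.** The point holds in a limited form. The estimate is meant to describe selection at approach but is collected after randomisation, when the ABPM has decided eligibility and the allocation may be known. It may not reflect the physician's belief at approach, and it omits patients excluded at t0. The descriptive selection check is therefore less reliable than it could be.

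Severity is minor. The randomised comparison of RH at 12 months, the sample size, alpha and power are untouched. A reader should not infer that the trial's main result is at risk.

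The verdict rests on one inference: that nothing outside the article keeps the allocation from the physician until the estimate is given. If such a step exists, the knowledge-of-arm part falls away. The ABPM, the elapsed time and the unrated exclusions remain.

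**What to change.** In Study design, replace the opening words that place the question after randomisation with: *At the t0 visit, before randomisation and, where possible, before the t0 ABPM result is available*. Apply this to all patients attending t0, and record the date of the estimate. Keep the existing requirement that it precede the report of drug levels.

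For patients already enrolled, record whether the allocation was known when the estimate was given, and report the check with that limitation.

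The cost is small: one question moves earlier, and estimates are also collected for some patients who are not randomised. Those extra estimates help, since they show the physician's view of patients whom the check now misses. A limit remains: even at t0 the estimate follows the invitation by at least a week, and it says nothing about patients who were never approached or who declined.
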